13.1 Definitions

| Term                 | Definition                                                                                                                                                                                                             |
|----------------------|------------------------------------------------------------------------------------------------------------------------------------------------------------------------------------------------------------------------|
| Safeguarding concern | Any issue that includes but is not necessarily limited to: 

• Self-reported immediate self-harm or suicide plans

• Self-reported immediate plans to harm others

 |

[figure not shown]

### 13.2 Reporting process

1. Within 24 hours of being made aware of safeguarding concern this should be reported to the trial team.
2. Where possible (i.e., access to the trial database) the individuals should directly complete a safeguarding form, however if reported by the Crisis CTI team, this should be reported to the trail team by phoning or emailing the trial administrator. No identifiable information should be used and participants should only be referred to by their PID number.
3. The trial team will review/enter details on the safeguarding form. Where external input is needed, i.e., probation officer etc. this will be sought.
4. Safeguarding forms will be reviewed by the Chief Investigator and signed off once appropriately resolved.
5. Safeguarding data will be collated onto a log by the Data Manager and reviewed at monthly TMG meetings.

## 14 Statistical considerations

### 14.1 Randomisation

Randomisation will be completed by a trial statistician on a 1:1 ratio and stratified by prison, using random blocks. A randomisation protocol will be developed separately and will include testing of the process and the system. Due to the restrictions of using electronic equipment during recruitment, randomisation will be completed using concealed paper envelopes. Each site will be provided with a box containing 60 sealed sequentially numbered envelopes (total 4 boxes). Envelopes will contain the arm allocation and PID number. Boxes and all envelopes will be clearly labelled with the prison name and sequence number. Training will be provided to site staff to outline the randomisation method. Prepared randomisation boxes will be checked by a member of the trial team to ensure the correct sequence is followed before being sent to sites. Randomisation method will be clearly documented in the randomisation protocol. Randomisation will be checked by TM or DM to ensure correct allocation.

### 14.2 Blinding

Allocations will be revealed after the baseline assessment, therefore at baseline participants and staff will be blind to group allocation. However, once randomised it will not be possible for participants or staff members to be blind as they will either receive the intervention or receive usual care. However, the trial statistician and health economist will remain blinded to group allocation during analysis. It will not be possible to blind the qualitative researcher.

[figure not shown]

### 14.3 Sample size

No power calculations have been performed as our aim is to evaluate acceptability of the intervention, not to estimate effectiveness. This study will determine rates of recruitment, response and retention, and the distribution of the indicative primary outcome measures in a full-scale RCT, to inform a full-scale trial sample size calculation. Given there is capacity to deliver the intervention to 120 participants per year, we aim to recruit 80 participants (40 per arm) which allows us to estimate a conservative recruitment rate of 50% within a 95% confidence interval (CI) of  $\pm 11\%$  (75% rate  $\pm 9.5\%$ ).

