| Development phase       | Phase II                                                                                                                                                                                                                                                                                                                                                                                                                               |
| Funder and ref.         | NIHR134281                                                                                                                                                                                                                                                                                                                                                                                                                             |
| Trial design            | Pilot Randomised controlled trial                                                                                                                                                                                                                                                                                                                                                                                                      |
| Trial participants      | Men at risk of homelessness leaving prison                                                                                                                                                                                                                                                                                                                                                                                             |
| Planned sample size     | 80 (1:1 randomisation intervention and usual care) allowing for 40% drop out at final follow-up                                                                                                                                                                                                                                                                                                                                        |

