## 5 Trial objectives/endpoints and outcome measures

The overall aim is to conduct a pilot RCT in four male prisons to determine whether a future full-scale RCT assessing effectiveness and cost-effectiveness of a housing-led CTI is warranted. The research questions are:

- 1 **Intervention and randomised trial delivery**
  - 1.1 Is the intervention acceptable to participants, those delivering and those funding?
  - 1.2 What do qualitative and quantitative data suggest in terms of refinements to programme theory, implementation, fidelity, reach, scalability, and acceptability?
  - 1.3 Are there potential harms and unintended consequences of the intervention? How might these be reduced? How can these be measured?
  - 1.4 Are there any potential ethical, practical, statutory, or other legal barriers in running a trial in this population?
- 2 **Recruitment**
  - 2.1 What proportion of eligible people in prison are recruited?
  - 2.2 What proportion of recruited participants are retained?
  - 2.3 What proportion of people in prison provide consent for linkage to routine health and criminal justice data?
- 3 **Data collection procedures**
  - 3.1 Are methods of data collection feasible and what refinements (if any) are needed?
  - 3.2 Are outcome measures suitable and what refinements (if any) are needed?
  - 3.3 What consent and governance requirements are acceptable to data providers for linkage to routine health, welfare, and criminal justice data?
  - 3.4 What are the likely sources of data on the health and broader social impacts of the intervention to inform an economic evaluation in a full-scale trial?

[figure not shown]

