### 5.1 Primary outcomes measure(s)

The primary outcome is progression criteria that will determine whether a full-scale RCT of the intervention is warranted. The progression criteria are:

- 1) Recruitment: 50% of those approached agree to participate.
- 2) Retention: 60% of those recruited, in both intervention and control groups, are retained at final follow-up.
- 3) The process evaluation provides evidence that the process is acceptable for participants and staff delivering the intervention.
- 4) The intervention is implemented with fidelity in all settings.

The progression criteria will be agreed in collaboration with an independent Trial Steering Committee (TSC), that will carefully consider progress against these criteria using thresholds for progression according to a traffic light system (green: all criteria are met, the study should progress as designed in this pilot; amber: the majority of criteria are met and with adaptations to methods all criteria could be met; red: the minority of criteria are met and the study should not proceed).

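### Section 14.3 computes recruitment-rate precision on the 80 people recruited instead of the people approached: ±11% and ±9.5% should be about ±7.7 and ±8.2 points

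*Protocol*

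**What the plan says.** Section 14.3 (Sample size) reports no power calculation. It mentions capacity to deliver the intervention to 120 people a year and then says "we aim to recruit 80 participants (40 per arm"), a number "which allows us to estimate a conservative recruitment rate of 50% within a 95% confidence interval" of ±11%, with ±9.5% in brackets for a 75% rate. These are the only precision figures in the protocol.

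The rate is defined elsewhere. The first progression criterion in section 5.1 reads "Recruitment: 50% of those approached agree to participate", and the synopsis also uses those approached. Research question 2.1 in section 5 asks "What proportion of eligible people in prison are recruited", which has a different denominator but again puts recruits on top.

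Two other statements bear on the point. The synopsis describes the 80 as "allowing for 40% drop out at final follow-up". The second progression criterion in section 5.1 is "Retention: 60% of those recruited, in both intervention and control groups, are retained at final follow-up".

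**The concern.** A recruitment rate is recruits divided by people approached (or by people eligible). The 80 in section 14.3 is the target number of recruits, so it cannot also be the denominator. If 80 people were approached and half agreed, the trial would have 40 participants, 20 per arm, which contradicts the 40 per arm in the same sentence.

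Recruitment is one of the two numerical progression criteria, and section 15.1 makes those criteria the primary analysis. The sentence is also the only statistical statement of what 80 participants will deliver. A figure in that position should describe the quantity it names.

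**Working it through.** **Inputs.** Recruits r = 80, rates p = 0.50 and 0.75, 95% confidence, and stated half-widths of 11 and 9.5 points (all section 14.3). The denominator of the rate is people approached (synopsis; section 5.1).

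**Formula.** Half-width = 1.96 × √(p(1 − p)/n).

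**1. Reproducing the stated figures with n = 80**
- p = 0.50: 1.96 × √(0.25/80) = 10.96 points, stated as 11.
- p = 0.75: 1.96 × √(0.1875/80) = 9.49 points, stated as 9.5.

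**2. Solving back for n = p(1 − p) × (1.96/half-width)²**
- From 11 points: 0.25 × (1.96/0.11)² = 79.4.
- From 9.5 points: 0.1875 × (1.96/0.095)² = 79.8.

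Allowing for rounding of 9.5 (9.45 to 9.55), n lies between 79.0 and 80.7. The other candidate numbers in the protocol do not fit:

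| n | Source | 50% rate | 75% rate |
|---|---|---|---|
| 40 | one arm | ±15.5 | ±13.4 |
| 48 | 80 less 40% drop-out | ±14.1 | ±12.3 |
| 80 | recruits | ±11.0 | ±9.5 |
| 120 | yearly capacity | ±8.9 | ±7.7 |

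So the denominator used was 80.

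**3. Precision with the defined denominator, n = 80/p**
- p = 0.50: n = 80/0.50 = 160, and 1.96 × √(0.25/160) = 7.7 points (Wilson interval for 80/160: 42.3% to 57.7%).
- p = 0.75: n = 80/0.75 = 106.7, about 107, and 1.96 × √(0.1875/106.7) = 8.2 points (Wilson interval for 80/107: 65.8% to 82.0%).

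**4. Why the ordering reverses.** Putting n = r/p into the formula gives a half-width of 1.96 × p × √((1 − p)/r). With r fixed at 80 this is 1.96 × 0.50 × √(0.50/80) = 7.7 points and 1.96 × 0.75 × √(0.25/80) = 8.2 points. A higher rate means fewer people approached, and between these two rates that outweighs the smaller binomial variance. The stated pair runs the other way, so its pattern is wrong as well as its size.

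**5. What the stated figures do describe.** They are correct for a proportion among 80 people. Retention of 60% in all 80 randomised, for example, has half-width 1.96 × √(0.24/80) = 10.7 points. In one arm of 40 it is 1.96 × √(0.24/40) = 15.2 points.

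**The case against.** The strongest reply is that nothing follows from the error. True recruitment precision is better than stated, the sample size does not change, and no threshold or analysis depends on the figures. The protocol offers 80 as a pragmatic pilot size, set beside delivery capacity and a drop-out allowance, and mentions the interval only as something that size permits. All of this stands, and it makes the point minor. It does not make the figures right: no definition of the recruitment rate in the protocol has 80 as its denominator.

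Two stronger readings are tempting, and the protocol supports neither.

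- A reader might infer that 80 has lost its justification or is too small. The error runs the other way, and neither the capacity figure nor the drop-out allowance is affected by it.
- A reader might infer that the protocol misstates, or wrongly hides, how uncertain the retention decision is. Section 14.3 gives no retention precision, so there is no wrong figure there. Planned precision for further feasibility outcomes can sit in the analysis plan, and section 15.1 already commits to 95% confidence intervals for all of them. Nor does retention alone decide progression: it is one of four criteria, two of them not numerical, which the steering committee weighs on a traffic-light scale. Reading the criterion per arm is natural from section 5.1, but the synopsis gives 60% of those enrolled without splitting by arm. On a pooled reading the half-width is 10.7 points, close to the printed 11.

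Whether recruitment should be counted against those approached or those eligible is a separate question of definition. The error exists under both.

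**Conclusion.** The stated precision is wrong for the quantity it names. With 80 recruits, a 50% recruitment rate would be estimated to about ±7.7 points instead of ±11, and a 75% rate to about ±8.2 instead of ±9.5. The protocol understates its recruitment precision by about 3.2 points (10.96 − 7.75) and 1.3 points (9.49 − 8.22), and it reverses which rate is the less precise.

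This rests on three assumptions: that the target of 80 recruits is met, that the number approached equals 80 divided by the rate, and that responses are independent with no clustering by prison. The arithmetic behind the stated figures is not in doubt.

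The point is a minor correction of a figure that errs on the cautious side. It gives no reason to change the design.

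**What to change.** Replace the precision sentence in section 14.3 with wording such as: *Recruiting 80 participants implies approaching about 160 people if 50% are recruited (95% CI ±7.7 points) or about 107 if 75% are recruited (±8.2 points).* Note beside it that 160 and 107 are derived and that clustering by prison is ignored.

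Alternatively, keep ±11% and ±9.5% and relabel them as the precision of a proportion of 50% or 75% among the 80 randomised.

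Optionally, add that 60% retention would be estimated to ±10.7 points overall (n = 80) and ±15.2 points in each arm (n = 40), because section 5.1 names both groups.

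The cost is one sentence of protocol text. The sample size, data collection, progression thresholds and analysis are unchanged.

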### 14.4 Missing, unused & spurious data

The rate of completeness for baseline and follow-up measures will be described. No imputation will be performed.

### 14.5 Procedures for reporting deviation(s) from the original SAP

Any deviations from the original statistical analysis plan (SAP) will be submitted as substantial amendments where applicable and recorded in subsequent versions of the protocol and SAP.

### 14.6 Termination of the trial

There will be no formal 'stopping rules' or 'discontinuation criteria' for individual participants, parts of study and entire study.

### 14.7 Inclusion in analysis

The trial population will be all participants who are eligible and consent to participate in the trial.

## 15 Analysis

### 15.1 Main analysis

The reporting of findings will be in accordance with the CONSORT guidelines for pilot RCTs [47]. The primary analysis of the pilot RCT will determine whether the prespecified progression criteria to a full-scale trial are met. All outcomes related to feasibility will be reported as point estimates with 95% confidence intervals (CIs).

Recruitment, baseline response, randomisation, follow-up at each time point, and consent to routine data linkage will be summarised in a CONSORT flow diagram. We will tabulate demographic characteristics of participants by study arm using descriptive statistics: means and standard deviations (SDs)(or medians and interquartile (IQR) ranges, as appropriate) for continuous outcomes, frequencies and percentages for categorical outcomes.

[figure not shown]

We will examine rates of completion of outcomes at each follow-up time point. We will pilot the analyses of effectiveness outcomes that would be done in a full-scale trial. Each outcome will be summarised at each time point (number (%), mean (SD), median (IQR)) and will be analysed in a separate multi-level regression model following the intention to treat approach and using data at baseline and follow up. The model will include fixed effects for intervention group, assessment time point (3, 6, 9, 12 months) and an interaction term between group and time. The model will allow us to examine the change in intervention over time compared to changes in the control arm. These estimates (odds ratios, mean differences) will be adjusted for participants nested within prison and will be presented alongside 95% CIs.

As this is a pilot trial, not powered for effectiveness, no hypothesis testing will be performed and no p-values presented. We will also estimate the clustering of outcomes within prisons and partial clustering of prisoners those imprisoning caseworkers (CTI arm only) by estimating intra-cluster correlation coefficients (with 95% CIs). Full details of the statistical analysis will be detailed in the statistical analysis plan (SAP). All analyses will be performed in Stata or R.

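### Section 15.1 names only prison clustering for the effect estimates and their CIs, although it recognises caseworker clustering in the CTI arm; a partially nested model should be reported alongside

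*Protocol*

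**What the plan says.** Four statements in protocol section 15.1 (Main analysis) bear on the point.

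- **Purpose:** "We will pilot the analyses of effectiveness outcomes that would be done in a full-scale trial".
- **Fixed part of the model:** "The model will include fixed effects for intervention group, assessment time point (3, 6, 9, 12 months) and an interaction term between group and time".
- **Clustering and precision of the effects:** "These estimates (odds ratios, mean differences) will be adjusted for participants nested within prison", with 95% CIs given for each.
- **Caseworkers:** in the following paragraph, the team will additionally estimate clustering within prisons and partial clustering for "caseworkers (CTI arm only) by estimating intra-cluster correlation coefficients (with 95% CIs".

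Prison therefore appears twice, in the adjustment of the effect estimates and in the list of ICCs. Caseworker appears only in the list of ICCs.

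The same section says that "no hypothesis testing will be performed and no p-values presented" and that "Full details of the statistical analysis will be detailed in the statistical analysis plan (SAP". That plan is not at hand.

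**The concern.** CTI is delivered by individual Crisis caseworkers. Section 11.1 describes relationship building, a tailored transition plan and nine months of phased support. Men who share a caseworker may therefore have correlated outcomes, and section 15.1 itself treats this as worth measuring. Usual care has no matching structure.

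A prison term does not take care of it. Randomisation is stratified by prison, so both arms are present in each prison and a shared prison effect largely cancels from the treatment contrast. Caseworker variance exists in the CTI arm only, so it stays in the contrast whether or not prison is modelled.

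Two things are at stake. With no p-values planned, the 95% CIs are the only inferential statement about effects. And section 15.1 is meant to rehearse the full-trial analysis, so whether a partially nested model can be fitted with few caseworkers is useful to learn now.

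**Working it through.** **The plan's own precision figure.** Section 14.3 gives a half-width of 11 points at a 50% rate and 9.5 points at 75%, with n = 80. Using 1.96 × √(p(1 − p)/80), I get 10.96 and 9.49 points, so both reproduce. They concern a proportion. The protocol states no precision for the effect estimates, so nothing below contradicts a stated figure.

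**Inputs from the protocol**
- 40 men per arm (section 14.3).
- 40% drop-out at final follow-up (Synopsis): 40 × 0.6 = 24 CTI completers.
- Five prisons (section 6).

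**Assumptions, because the protocol gives neither value**
- Number of caseworkers k: 4 to 8. The nearest figure is the six interventionists to be interviewed (section 6), which is an interview sample and not a headcount.
- Caseworker ICC: 0.01 to 0.10.
- Equal caseloads, equal total variance in the two arms, one time point.

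**Formulas.** With n men in the CTI arm and caseload m = n/k:
- CTI-arm design effect: DE = 1 + (m − 1) × ICC. The control arm has DE = 1.
- True SE over reported SE: r = √((DE + 1)/2).
- True coverage of a nominal 95% CI: 2Φ(1.96/r) − 1.

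**Results**

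| CTI men | k | m | ICC | DE | r | Coverage |
|---|---|---|---|---|---|---|
| 24 | 8 | 3.0 | 0.01 | 1.02 | 1.005 | 94.9% |
| 24 | 6 | 4.0 | 0.01 | 1.03 | 1.007 | 94.8% |
| 24 | 6 | 4.0 | 0.05 | 1.15 | 1.037 | 94.1% |
| 24 | 6 | 4.0 | 0.10 | 1.30 | 1.072 | 93.2% |
| 24 | 4 | 6.0 | 0.10 | 1.50 | 1.118 | 92.0% |
| 40 | 8 | 5.0 | 0.01 | 1.04 | 1.010 | 94.8% |
| 40 | 6 | 6.67 | 0.05 | 1.28 | 1.068 | 93.3% |
| 40 | 4 | 10.0 | 0.10 | 1.90 | 1.204 | 89.6% |

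At ICC = 0, r = 1 and nothing changes.

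**Does a prison term absorb it?** This was checked by simulation: five prisons, caseworkers nested in prison in the CTI arm only, a single-time-point linear model with fixed prison effects standing in for the prison random intercept, and 4,000 runs per setting. With 40 per arm and one caseworker per prison, r was about 1.05, 1.10 and 1.18 at ICC 0.02, 0.05 and 0.10, with coverage 93.8%, 92.9% and 90.6%. The formula for k = 5 gives 1.03, 1.08 and 1.16. With two caseworkers per prison and ICC 0.10, r was 1.09 and coverage 93.5%. At ICC 0, where r should be 1, the simulated values ran from 0.99 to 1.03, so differences of a few hundredths are noise. The prison term does not remove the problem.

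**How well could the caseworker variance be estimated?** In a balanced one-way normal model, the ANOVA estimate is zero or negative when a central F variable on k − 1 and n − k degrees of freedom falls below 1/(1 + m × ICC/(1 − ICC)). For k = 6 and n = 24 this has probability 45% at ICC 0.05 and 36% at 0.10. For n = 40 it is 40% and 28%.

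**The case against.** The strongest reply is that nothing here is fixed wrongly. Section 15.1 never says prison is the only level, estimating a caseworker ICC already needs caseworker variance to be modelled in some form, and full details go to the SAP. The section proposes to measure the caseworker ICC and does not assert that it is positive. The trial is not powered for effectiveness, and progression rests on recruitment, retention, acceptability and fidelity (section 5.1). Finally, with few caseworkers the variance will often be estimated at zero, and the interval would then be about the same as the prison-only one.

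Much of this stands. A reader might infer that the protocol rules out a caseworker level, that its CIs are too narrow as a matter of fact, or that the piloted model is not the one a full trial would need. The text supports none of these. It excludes no level, the narrowing requires an ICC above zero, and measuring that ICC is how the pilot would inform the later choice. Nor is it shown that the pilot fails to try a partially nested model, since the source of the ICC is not stated.

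What remains is narrower. The protocol does state the clustering adjustment for the effect estimates, and it names prison alone. This is a stated method that can be improved, not just a detail left to the SAP. The risk of a zero variance estimate argues for showing both models, not for omitting the second.

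**Conclusion.** The point holds in conditional form. As described, the effect estimates and CIs carry prison clustering, while caseworker clustering is measured but not carried into them. If the caseworker ICC is above zero and the model has no caseworker level, the true SE exceeds the reported SE by about 1% to 12% with 24 CTI completers. The 20% figure, with coverage of 89.6%, needs full retention, 4 caseworkers and an ICC of 0.10 together, and should not be taken as typical. All of these sizes rest on assumed caseworker counts and ICCs.

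This is a cheap improvement, not an error that threatens the trial. No tests are planned and no progression decision uses these intervals. The main gain is learning whether the partially nested model can be fitted.

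**What to change.** Add one sentence to section 15.1, carried into the SAP: the effect estimates and 95% CIs will also be reported from a partially nested model with a caseworker random effect in the CTI arm only. This should be the same model that supplies the caseworker ICC, shown alongside the prison-only model. Add that non-convergence or a zero estimate of caseworker variance will be reported as a feasibility result.

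The cost is small. The planned caseworker ICC already needs the caseworker identifier and a caseworker variance component, so no new data are required. The downside is an unstable variance estimate with few caseworkers. The second interval should therefore be read as a check on the first, without a claim that it restores exact 95% coverage.
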